##### 4b. Secondary objectives

1. For non-pregnant adults, compare the cost per patient alive, in care, and virally suppressed within 10 months of an HIV test or enrollment in HIV care for those offered rapid ART initiation to the cost for those offered standard care.
2. For pregnant women, estimate the cost per patient adhering to ART through delivery and the cost per infant infection avoided, using estimated vertical transmission rates.
3. Estimate the proportion of patients alive, on ART, and virally suppressed at 6 month intervals after treatment initiation and at the final date of data censoring.
4. Estimate the average time interval between HIV test or first HIV or ANC care visit and treatment or PMTCT initiation before and after rapid ART initiation became the guideline procedure for pregnant women.
5. If enrollment numbers allow, among pregnant women, stratify the primary outcome (the proportions of subjects achieving retention on ART or PMTCT regimen until delivery) by CD4 count > 350 and  $\leq 350$ .
6. Compare the average gestational age at ART initiation and average number of weeks on ART prior to delivery for pregnant women before and after rapid ART initiation became available.
7. Identify patient-level predictors of treatment uptake, retention in care, and viral suppression.
8. Describe the prevalence of TB symptoms and confirmed TB, time to initiation of TB treatment, and time to initiation of ART among patients with TB.
9. Evaluate the feasibility of the rapid initiation strategy in terms of patient acceptance, actual time between HIV test/enrollment in care and dispensing of first dose of ARVs, and patient costs incurred.

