##### *6c i. Rapid CD4 count and TB symptom screen*

The first step for rapid initiation will be a venous blood draw for a rapid CD4 count (and for other treatment initiation tests for those found eligible for treatment). For those offered rapid initiation, the blood sample will be processed immediately, on site, using the Pima Analyzer, rather than being stored for later transport to an off-site laboratory. The processing time for the Pima test is 20 minutes. In a validation study of Pima used at point of care clinics in South Africa, 7-9% of tests could not be read or had invalid results, due primarily to user errors in obtaining blood samples or filling cartridges. Careful training will be provided to study staff to minimize this type of error. A second Pima test will be run for subjects for whom the first Pima result is invalid. In addition, a blood sample will be sent to the off-site National Health Laboratory Service (NHLS) laboratory for all subjects in the rapid group for a confirmatory CD4 count. NHLS lab results will be monitored by the study team, and any subject found

not eligible for treatment using Pima but eligible based on lab results will be contacted by the study assistant and asked to return to the clinic to initiate treatment following rapid initiation procedures.

Patients who already have with them a valid CD4 count result (sample taken within the previous 6 months) will not have an additional CD4 count, though a blood sample will still be drawn for other required laboratory tests.

While awaiting CD4 test results, the study nurse will administer a TB symptom screen following South African guidelines for the definition of symptoms, for all subjects not already on TB treatment. Subjects with any TB symptoms will be asked to provide a sputum sample. The study nurse will also ask the subject about symptoms that might indicate a Stage 4/3 condition. Subjects who report such symptoms will be given a physical examination to determine if the condition exists and what treatment is needed.

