#### *6c ii. TB test*

Sputum samples for patients with TB symptoms will immediately be sent to the on-site laboratory for testing using Xpert MTB/RIF. Each patient will be asked for two sputum samples to allow two Xpert tests to be run. Those with at least one positive Xpert test will be considered to have active TB. Those with two negative tests will be considered not to have TB. Those with inconclusive test results will be diagnosed clinically by the study nurse or the site doctor. Patients diagnosed with TB will be told of their results and escorted by the study assistant to the site's TB clinic, where TB treatment can be initiated.

A third sputum sample for all patients diagnosed with TB will be sent to the off-site National Health Laboratory Service laboratory for smear microscopy and culture if required. The NHLS lab results will be monitored by the study team. Any positive TB diagnosis not already made by the study nurse will be conveyed immediately to the site, and the patient will be contacted by the study assistant and asked to return to the clinic to initiate TB treatment.

The study site's standard procedures will be followed with regard to TB treatment. Under current South African guidelines, two weeks (14 days) of TB treatment is required prior to initiating ART for patients with a CD4 count  $\leq 350$  and eight weeks of TB treatment is required for patients with a CD4 count  $> 350$ . Study subjects diagnosed with TB and with CD4 counts  $\leq 350$  will be asked to return to the clinic between 14 and 28 days after study enrollment to continue with rapid ART initiation. Those returning in more than 28 days will be offered standard ART initiation. Subjects with TB and CD4 counts  $> 350$  will be advised to return for TB treatment only, then continue with standard ART initiation. Patients already on TB treatment but for less than 14 days at the time of study enrollment will also be asked to return once they have reached 14 days of TB treatment.

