#### *6d ii. Remaining ART readiness and initiation steps*

Subjects who are eligible for treatment will follow the site's standard procedures for initiating ART, based on South African guidelines. These include 1-3 return visits to the clinic for remaining laboratory tests (creatinine, full blood count, ALT, pregnancy, syphilis), TB diagnosis and treatment if required, adherence counseling, wellness education, and a physical exam. Medications will then be prescribed by the site doctor or primary health care nurse and dispensed by the site's pharmacy.

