#### *11a ii. Secondary outcomes*

Secondary outcomes will include:

1. Average cost per patient who is alive, in care, and virally suppressed within 10 months of study enrollment (Track 1).
2. Cost per patient adhering to ART through delivery and the cost per infant infection avoided, using estimated vertical transmission rates (Track 2).
3. Proportion of subjects in each track and group alive, on ART, and virally suppressed at six-month intervals and the final date of data censoring.
4. Average time to ART initiation (days) for each track and group.
5. For Track 2, average gestational age at ART initiation (weeks) and average duration (weeks) on ART prior to delivery.
6. For Track 2, if enrollment numbers allow, proportion of subjects with CD4 count > 350 and ≤ 350 achieving the primary outcome of retention on ART (or PMTCT regimen) until delivery.
7. Patient-level predictors of treatment uptake, retention in care, and viral suppression.
8. Prevalence of TB symptoms and confirmed TB, time to initiation of TB treatment, and time to initiation of ART among patients with TB.
9. Process indicators including:
  - Acceptance of rapid initiation strategy (% of patients offered rapid initiation who accept)
  - Average time elapsed (days) between HIV test and dispensing of first dose of ARVs
  - Average cost to patients of initiating treatment, including travel and other out-of-pocket costs and time spent in clinic

All outcomes will be estimated for each study population and compared between the two study populations where relevant.

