#### 11b. Clinical outcomes analysis

For both tracks and for primary and secondary clinical outcomes, the analytic approach for clinical outcomes will be the same. All analyses will be by intention-to-treat: subjects will be analyzed according to the intervention they were supposed to receive, whether or not they adhere to the defined intervention.

The analysis will begin with a simple comparison of the two treatment groups with respect to baseline predictors of outcomes. We will then conduct a crude analysis comparing the proportion of patients achieving each dichotomous outcome by group and crude risk ratios and 95% confidence intervals

stratified by group. For average gestational age at ART initiation and average time on ART before delivery for Track 2, we will calculate the mean difference between groups and corresponding 95% confidence interval.

Since adherence has been a particular concern for pregnant women who were not eligible for ART under the previous guidelines, the primary outcome for Track 2 will be stratified in secondary analysis by CD4 count at the time of initial ANC visit if enrollment numbers by the end of the study period are large enough to allow a stratified analysis. Subjects in the prospective group found after ART initiation to have CD4 counts above 350 will be compared to those in the retrospective group who were offered AZT under the previous guidelines, while subjects in the prospective group found after ART initiation to have CD4 counts below 350 will be compared to those in the retrospective group who were offered full ART under the previous guidelines.

Because we will not be randomizing large numbers of patients in Track 1 and because no randomization will occur in Track 2, it is possible that some baseline covariates may be imbalanced by treatment arm. To adjust for potential differences by baseline covariates, a log-linear regression model will be used to estimate adjusted risk ratios and a linear regression will be used to adjust mean differences.

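### Secondary outcome 8 (TB prevalence and times among TB patients) is not limited to an arm, yet TB is sought systematically only in the rapid arm, so a by-arm or pooled figure would mix detection with prevalence

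*Protocol*

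**What the plan says.** Item 8 of section 11a ii (Secondary outcomes) is "Prevalence of TB symptoms and confirmed TB, time to initiation of TB treatment, and time to initiation of ART among patients with TB". It names no arm. The matching objective in section 4b is worded as a description: "Describe the prevalence of TB symptoms and confirmed TB, time to initiation of TB treatment, and time to initiation of ART among patients with TB".

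Section 11b (Clinical outcomes analysis) states that the approach is the same for primary and secondary clinical outcomes and that all analyses are by intention to treat. It plans a "crude analysis comparing the proportion of patients achieving each dichotomous outcome by group", with crude risk ratios and 95% confidence intervals. It exempts no secondary clinical outcome.

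TB is looked for differently in the two arms:

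- **Rapid arm.** Under section 6c i the nurse's task, during the wait for the CD4 result, is to "administer a TB symptom screen following South African guidelines for the definition of symptoms, for all subjects not already on TB treatment". Under section 6c ii, which covers those with symptoms, "Each patient will be asked for two sputum samples to allow two Xpert tests to be run".
- **Standard arm.** Section 6d ii places TB diagnosis and treatment, where required, among the site's usual initiation steps: "These include 1-3 return visits to the clinic for remaining laboratory tests", and the list goes on to TB work-up, counselling and examination. Section 6b iv says the study team has no personal contact with this group after randomization, and that these subjects go on to a standard pre-ART visit that day. Section 8e takes follow-up data from routine records. It lists the TB screen and test fields under the baseline at ART initiation, and notes that electronic records typically exist only once ART has started, with paper files as a supplement.

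**The concern.** Active TB detection is part of the rapid strategy. In the standard arm, whether TB is found depends mostly on the subject coming back and on what routine care records, and return is the behaviour that the intervention is meant to change.

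Three consequences follow if item 8 is analysed as section 11b reads.

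- A between-arm risk ratio for TB symptoms or confirmed TB reflects who was assessed as well as who had TB.
- A pooled prevalence over all enrolled subjects is pulled down by the standard arm.
- Times to TB treatment and to ART among patients with TB set all cases found by the rapid-arm work-up against those standard-arm cases that routine care picked up, who are likely to be the better retained. Randomization does not protect that comparison, because membership of the subset is decided after randomization by a process that differs by arm.

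Restricting the standard arm to subjects with a recorded screen removes the denominator problem but still selects largely those who returned.

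**Working it through.** The Protocol gives no TB prevalence by arm, so it has no figure of its own to reproduce here. The calculation shows how large the distortion could be.

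**Inputs**

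- Subjects per arm: 400 enrolled at 1:1 (section 10), so 400 / 2 = 200.
- True TB prevalence p: 15% in both arms, an assumption. Section 3b says fewer than 20% of HIV patients have TB. The range shown is 10% to 20%.
- Share c of standard subjects assessed for TB: an assumption, with two anchors in the Protocol.
  - Section 3a reports that 49% of eligible patients in earlier work did not return for CD4 results within 3 months, so c = 1 − 0.49 = 0.51.
  - Section 10 plans for 50% of the standard arm to be suppressed by 10 months and cites 77% suppression among those in care. That implies 0.50 / 0.77 = 0.65 started ART and so went through the pre-ART steps.
  - 75% and 90% are added to show better coverage.
- Unassessed standard subjects are counted as TB-negative, and assessment is unrelated to TB status. Both are assumptions.

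**Formulas**

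- Recorded standard-arm prevalence = p × c
- Pooled prevalence = p × (1 + c) / 2
- Spurious risk ratio, rapid to standard = p / (p × c) = 1 / c
- Chance of p<0.05 = probability that a two-sided two-proportion test (normal approximation, 200 per arm) rejects in favour of more TB in the rapid arm

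**Results at p = 15%**

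| Share assessed | Standard arm records | Pooled | Risk ratio | Chance of p<0.05 |
|---|---|---|---|---|
| 51% | 0.15 × 0.51 = 7.65% | 11.3% | 1.96 | 64% |
| 65% | 0.15 × 0.65 = 9.75% | 12.4% | 1.54 | 36% |
| 75% | 0.15 × 0.75 = 11.25% | 13.1% | 1.33 | 20% |
| 90% | 0.15 × 0.90 = 13.5% | 14.3% | 1.11 | 6% |

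At true TB of 10% and 20% the risk ratios are unchanged. The chance of p<0.05 becomes 46% and 78% at 51% assessed, 25% and 47% at 65%, 14% and 26% at 75%, and 5% and 7% at 90%.

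**TB symptoms.** These are commoner, so the same shortfall shows more clearly. At the upper figure of 70% in section 3b, 80% assessed gives 0.70 × 0.80 = 56% recorded and an 83% chance of p<0.05. At 90% assessed it gives 63% and 32%.

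**Times among TB patients.** No figure can be put on these from the documents. The argument is the selection described above.

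**The case against.** The case on the other side is substantial.

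- **The comparison is not spelled out.** The objective says describe, and items 3 and 4 of section 11a ii specify each track and group while item 8 does not. The closing line of that section compares study populations only where relevant. This stands as a reason to rate the point low. It does not remove it, because section 11b covers all secondary clinical outcomes without exception and a pooled description is affected too.
- **Unscreened subjects need not be counted as TB-negative.** A reader might infer that the plan does this. It does not say so: section 11a i states a missing-equals-failure rule for the primary outcome, and there is none for TB. Dates and results of TB screens and tests are collected (section 8e), so a screened-only denominator is possible. This stands, and the table therefore depends on that assumption.
- **A reader might infer that standard subjects are assessed only if they return.** That is too strong. They have a standard pre-ART visit on the day (section 6b iv) whose TB content is not described. The study team monitors their TB results (section 6b vi) and reviews paper files monthly (section 8f ii). Some are recruited when they have already come back for a CD4 result (section 6b i). Nor is every rapid subject screened: those already on TB treatment are not, though their TB is known.
- **The 51% row is not the best guess.** It comes from a 3-month return figure in earlier work, while follow-up here is 10 to 24 months. The Protocol's own planning figures point to about 65% starting ART, and subjects who return but never start would raise coverage further.
- **TB detected under each strategy is worth reporting by arm.** Rapid TB testing is part of the strategy (section 5a). This stands, and a ban on all between-arm figures would go too far.

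**Conclusion.** The asymmetry in ascertainment is in the text and item 8 does not allow for it. Analysed by group or pooled over all enrolled subjects, it would tend to understate TB in the standard arm, and the times among TB patients would compare differently selected groups.

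The size is uncertain. At equal true TB of 15%, the Protocol's planning figures suggest a spurious risk ratio of at most about 1.54, with a 36% chance of a false p<0.05. The ratio of 1.96 belongs to the pessimistic end, and good coverage shrinks it to 1.11. All of these require unassessed subjects to be counted as TB-negative, assessment to be independent of TB status, and true prevalence to be equal among those enrolled. The last may not hold exactly, since a TB diagnosis is itself a route to enrolment (section 6b vi).

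The documents do not support saying that the plan records unscreened subjects as free of TB, or that the arms must never be set side by side. The primary outcome, the sample size and the interim rule are not affected. This is a minor point on a descriptive secondary outcome.

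**What to change.** In section 11a ii, item 8, and in section 11b:

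- Estimate the prevalence of TB symptoms and of confirmed TB from the rapid arm, where screening is systematic and those already on TB treatment are known cases.
- For the standard arm, report the number and share of subjects with a recorded TB screen, and the TB detected among them.
- Label any between-arm figures, including times to TB treatment and to ART among TB patients, as descriptive of TB detected under each strategy. State that they are excluded from the risk-ratio comparison as estimates of prevalence or effect.

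This takes a sentence or two in each section and changes no study procedure. The cost is precision: prevalence rests on about 200 rather than 400 subjects. At 15% the 95% half-width is 1.96 × √(0.15 × 0.85 / 200) = 4.9 percentage points, against 1.96 × √(0.15 × 0.85 / 400) = 3.5.

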#### 11b. Clinical outcomes analysis

For both tracks and for primary and secondary clinical outcomes, the analytic approach for clinical outcomes will be the same. All analyses will be by intention-to-treat: subjects will be analyzed according to the intervention they were supposed to receive, whether or not they adhere to the defined intervention.

The analysis will begin with a simple comparison of the two treatment groups with respect to baseline predictors of outcomes. We will then conduct a crude analysis comparing the proportion of patients achieving each dichotomous outcome by group and crude risk ratios and 95% confidence intervals

stratified by group. For average gestational age at ART initiation and average time on ART before delivery for Track 2, we will calculate the mean difference between groups and corresponding 95% confidence interval.

Since adherence has been a particular concern for pregnant women who were not eligible for ART under the previous guidelines, the primary outcome for Track 2 will be stratified in secondary analysis by CD4 count at the time of initial ANC visit if enrollment numbers by the end of the study period are large enough to allow a stratified analysis. Subjects in the prospective group found after ART initiation to have CD4 counts above 350 will be compared to those in the retrospective group who were offered AZT under the previous guidelines, while subjects in the prospective group found after ART initiation to have CD4 counts below 350 will be compared to those in the retrospective group who were offered full ART under the previous guidelines.

Because we will not be randomizing large numbers of patients in Track 1 and because no randomization will occur in Track 2, it is possible that some baseline covariates may be imbalanced by treatment arm. To adjust for potential differences by baseline covariates, a log-linear regression model will be used to estimate adjusted risk ratios and a linear regression will be used to adjust mean differences.

Variables considered to be important in the univariate stage will be included in multivariate models. Adjusted analyses will include covariates which are unevenly distributed across groups and which could plausibly affect viral suppression or time to ART initiation. These potential confounders include demographic (e.g. age, sex) and socioeconomic (education, distance from clinic, employment, etc.) variables, medications, baseline CD4 counts, prior receipt of PMTCT, and low BMI, among others. Each of these models can then be used to look for patient-level predictors of treatment uptake, viral suppression, and retention in care.

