#### 8e. Medical record data

Most data for the study will be collected from the site's routinely maintained electronic medical records, which are maintained in an information system called Therapy Edge-HIV™. Records in this information system are typically only created once a patient starts ART. Paper-based medical records kept by the site will therefore be used to supplement the electronic medical record system as needed. The fields to be collected are listed below.

*To be used to link electronic and paper-based records to study identification number only:*

- Electronic medical record system number
- Clinic file numbers
- National ID number
- Name
- Date of birth

*All subjects at baseline (ART initiation):*

- Date of positive HIV test (if available)
- Sex
- Age in years
- Weight and height or BMI
- Date treatment eligibility determined, if reported
- Date and result of eligibility-determining CD4 count
- Date and result of TB symptom screen
- Date, type, and result of TB test(s)
- TB treatment, if relevant
- WHO stage and clinical conditions
- Date ART initiated (first dose of drugs dispensed)
- First-line regimen prescribed

*For all clinic visits for duration of study follow up, including initial visit and pre-ART visits (to be used to estimate resource utilization):*

- Date of visit
- Primary reason for visit (e.g. scheduled medical visit, medication pickup, unscheduled medical visit)
- Types of professionals seen (e.g. nurse, doctor, pharmacy assistant, counselor)
- Group and individual sessions attended (e.g. wellness course, adherence education)
- Numbers and types of all lab tests conducted (including CD4 counts and viral loads)
- Other procedures (e.g. x-rays) performed

- Medications prescribed and dispensed (ARV and non-ARV)
- Admissions for inpatient care since previous visit, if recorded
- Details of inpatient care received (facility, number of days, medications, lab tests, etc.) if recorded

*At interim and final dates of data censoring:*

- Date and result of most recent viral load test
- Status at clinic (in care / died / transferred to another site / stopped care / lost to follow up, defined as > 1 month late for last medication pickup)
- New or recurring HIV-related conditions
- Date and cause of death if applicable
- Date and result of most recent CD4 count

*Track 2 subjects only (pregnant women):*

- Gestational age at diagnosis or first ANC visit for current pregnancy if previously diagnosed
- Prior exposure to PMTCT

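### The Track 2 CD4-stratified comparison sorts prospective women by CD4 result but retrospective women by regimen offered, so the two sides of each stratum are selected by different rules

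*Protocol*

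**What the plan says.** Secondary objective 5 (Protocol 4b) is, if numbers allow, to "stratify the primary outcome (the proportions of subjects achieving retention on ART or PMTCT regimen until delivery) by CD4 count > 350" and ≤ 350. Secondary outcome 6 (11a ii) repeats it as the proportion in each of those two CD4 ranges "achieving the primary outcome of retention on ART (or PMTCT regimen) until delivery". Neither place treats the two groups differently.

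Section 11b says the Track 2 primary outcome will be "stratified in secondary analysis by CD4 count at the time of initial ANC visit if enrollment numbers" permit. The next sentence puts this into practice. "Subjects in the prospective group found after ART initiation to have CD4 counts above 350" are one side of the upper stratum, and they "will be compared to those in the retrospective group who were offered AZT under the previous guidelines". Prospective women below 350 are "compared to those in the retrospective group who were offered full ART under the previous guidelines".

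The same section opens with an intention-to-treat rule for all analyses: "subjects will be analyzed according to the intervention they were supposed to receive, whether or not they adhere to the defined intervention". Section 11a i starts the Track 2 analysis period at study enrollment, not at ART start. Section 8e lists "Date and result of eligibility-determining CD4 count" among the baseline record fields.

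**The concern.** A stratified pre/post comparison is interpretable only if a woman would fall in the same stratum whichever period she attended in. Here a prospective woman is placed by a laboratory result and a retrospective woman by a clinic decision. The decision depended on CD4, but section 10 describes starting CD4 only as a criterion for treatment in the earlier period. It does not say that every offer tracked the result.

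The wording also makes membership depend on events after enrollment: starting ART in one group, receiving an offer in the other. Women who fail at that step are non-adherent under the primary outcome. If they leave the strata unequally between groups, a difference can appear when adherence has not changed.

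The analysis is secondary, but the plan gives it weight. Section 11b calls adherence a particular concern in women who were not previously eligible, and section 10 justifies enlarging Track 2 from 152 to as many as 305 women so that it can be done.

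**Working it through.** **The plan's own figure.** Section 10 gives 76 per group for 77% versus 96% at 5% alpha and 90% power. A two-sided normal-approximation calculation gives 77 with continuity correction and 66 without. Exact Fisher power at 76 per group is 93.2%. The stated size is therefore adequate and is not in dispute. The protocol gives no figure for the stratified comparison itself.

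**The definitions side by side.**

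| Place | Prospective women | Retrospective women |
|---|---|---|
| 4b objective 5; 11a ii item 6 | CD4 > 350 / ≤ 350 | CD4 > 350 / ≤ 350 |
| 11b, stratifier as named | CD4 at first ANC visit | CD4 at first ANC visit |
| 11b, as carried out | CD4 result known after ART start, above / below 350 | Offered AZT / offered full ART |

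The third row departs from the first two. Followed literally, three sets of women have no stratum: prospective women who never start, retrospective women offered neither regimen, and prospective women with a CD4 of exactly 350.

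**Effect of losing women from a stratum.** Let true adherence among all women in a CD4 range be A in both groups, so there is no real change. Let a share d of prospective women (never started) and a share r of retrospective women (never offered) be dropped, all of them non-adherent. The observed rates are then

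- prospective: A / (1 − d)
- retrospective: A / (1 − r)
- spurious risk ratio: (1 − r) / (1 − d)

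The documents give neither d nor r, so the values below are assumptions. A = 77% is borrowed from section 10 for illustration only; there it is a proxy among women who had started ART. The 12% echoes the cited Cape Town pilot (section 3c: 89 of 101, or 88%, started the same day). That is same-day non-start, not never-start.

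| d | r | Prospective | Retrospective | Difference | Risk ratio |
|---|---|---|---|---|---|
| 5% | 0 | 0.77/0.95 = 81.1% | 77.0% | +4.1 points | 1.05 |
| 12% | 0 | 0.77/0.88 = 87.5% | 77.0% | +10.5 points | 1.14 |
| 12% | 12% | 87.5% | 87.5% | 0 | 1.00 |
| 5% | 12% | 81.1% | 87.5% | −6.4 points | 0.93 |
| 0 | 12% | 77.0% | 87.5% | −10.5 points | 0.88 |

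The sign depends only on whether d exceeds r.

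**Effect of misplacing women between strata.** If a share m of a retrospective stratum belongs to the other CD4 range and adherence there differs by g, the stratum rate shifts by m × g. Assumed values of m = 5% and g = 5 points give 0.25 points; m = 20% and g = 20 points give 4 points. The sign of g is unknown as well.

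**The case against.** The phrase about results found after ART initiation most naturally says when the result becomes known. The preceding sentence names CD4 at the first ANC visit, and ART is to start at that visit (sections 5a and 7). A reader might infer that the plan stratifies on a CD4 sampled after treatment began; the text does not support that.

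No passage expressly excludes non-starters. Enrollment as the start point and the intention-to-treat rule both point towards keeping them. This stands as a reason to read the clause generously. It does not tell an analyst which stratum a non-starter enters, and the record system does not help: section 8e heads its baseline fields as ART initiation, and section 8f ii says electronic records are created only once ART starts.

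Regimen offered can be defended as a marker of prior eligibility, which is the reason section 11b gives for the analysis. No passage reports an offer that departed from CD4. Section 3a says 49% of eligible patients at a Johannesburg facility did not return for CD4 results within 3 months, but these were general outpatients, so the evidence is indirect. How well offer tracked CD4 in this clinic is unknown. That does not reconcile the two definitions.

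The boundary at 350 is a wording slip, since 4b and 11a ii both use ≤ 350. The analysis is also secondary, non-randomized and conditional on enrollment.

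**Conclusion.** The inconsistency is certain: section 11b carries out the stratified analysis with a different variable in each group, against its own named stratifier and against 4b and 11a ii. It follows that the within-stratum pre/post comparison can be biased. Size and sign are not determined. The ±10.5 points shown rest on assumed losses of 12% from one group only and on A = 77%; equal losses give no bias from this source.

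A reader might infer that the prospective result is inflated, for example by 77% − (0.88 × 0.77 = 67.8%) = 9.2 points. The documents do not support that. It requires non-starters to be dropped, which is nowhere stated. It treats same-day non-start in a pilot as never starting. It also ignores that requiring an offer can remove failures from the retrospective side in the same way.

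The Track 2 primary comparison does not use these strata and is unaffected. The point is worth correcting because a common rule removes the selection difference at little cost.

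**What to change.** In 11b, replace the group-specific sentence with one rule for both groups:

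- Stratify by the CD4 result from the first ANC visit, or the nearest one before it, as > 350 versus ≤ 350, regardless of regimen offered or whether treatment started.
- Keep every enrolled woman; count those who never start as not adherent.
- Show women with no CD4 result as a separate row in each group.
- Report regimen offered descriptively, or as a sensitivity analysis for the prior-eligibility question.

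The cost is mainly wording. CD4 is already expected in the data: 8e lists it and 11b names baseline CD4 as a candidate covariate. The 8e field should be reworded to cover the first-ANC CD4 for all Track 2 women. Its present label refers to the count that determined eligibility, yet section 5c makes all HIV-positive pregnant women eligible. For retrospective women who never started, the result must be sought in paper records and registers. Some will have none and cannot be stratified.
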